### Intervention

#### Development of intervention components

As the study is currently in year 1, we are developing, piloting, and validating the following study materials to be used in the intervention: a diagnostic algorithm for CAUTI versus ABU, the audit and feedback script and intervention, and the pre/post surveys (described in Data collection below) of guidelines knowledge and attitudes (see Tables 1 and 2).

**Table 2 T2:** outcome measures for objective 2

Outcome	Measurement strategy	Measure of meaningful change
Guidelines awareness	Survey questions KA1-KA2^a^	Raw number and proportion of respondents changing from NO to YES

Guidelines familiarity	Survey question KF1 ^a^	Average increase from "do not recall" or "minimal recall" to "working familiarity" or "complete recall"

Guidelines familiarity	Survey questions KF2-KF8	Raw number and proportion of respondents changing from SD or D to SA or A

Guidelines familiarity	Survey question KF9	Raw number and proportion of respondents changing from incorrect to correct answers

Guidelines acceptance	Survey questions AA1-AA2 ^a^	Raw number and proportion of respondents changing from SD or D to SA or A

Outcomes expectation	Case scenarios OE1-OE6	Raw number and proportion of respondents changing from incorrect to correct answers

Implementation performance measures	Qualitative exit interviews	≥75% positive statements
	Capture of episodes of bacteriuria	≥95% capture of episodes of bacteriuria
	Delivery of audit and feedback	≥80% delivery to correct provider

^a^KA measures knowledge awareness, KF measures knowledge familiarity, AA measures awareness acceptance, and OE measures outcome expectancy.

A = agree; D = disagree; SA = strongly agree; SD = strongly disagree.

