The survey instrument will have three sections. The first section will be a cover letter. The cover letter explains the purpose of the study to the healthcare providers and explains that their participation is entirely voluntary, thus satisfying implied consent for participation. The second part of the survey is a cover sheet that assesses provider demographics, such as level of training, type of training, etc. This cover sheet will have a randomly generated number on it that will also appear on each subsequent sheet of the survey. The cover sheet with the provider's identifiable information can then be separated from the surveys to avoid bias in interpretation of survey results. The third section of the survey contains the survey questions. These questions will assess knowledge: degree of awareness of the existence of the guidelines, familiarity with the guidelines' content, and confidence in that familiarity. Other questions will measure physicians' acceptance of the guidelines, and we have also designed short patient scenarios to assess outcome expectancy about the guidelines. Each case will present a hospitalized patient with bacteriuria and a chronic, indwelling urinary catheter. The cases will differ in elements, such as the level of pyuria, the patient's age and comorbidities, the type of organism isolated from the urine, the appearance or smell of the urine, the presence of specific urinary symptoms, and the presence of vague systemic complaints. Providers will be asked whether they would or would not treat each case with antibiotics. These cases are designed to address providers' beliefs about the consequences of not treating bacteriuria (risk perception) and to elucidate which elements drive the decision to treat/not treat bacteriuria.

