Although we have built our survey on established models concerning antibiotic prescribing decisions, [29] our survey instrument has been tailored to our specific clinical issue (CAUTI) and, thus, will require pilot testing with a selection of participants from the targeted groups of healthcare providers. We plan to conduct cognitive interviews to assess clarity of wording, understandability of items, and appropriateness of response options. We will conduct preliminary analyses of responses given, response-option use frequency, and floor/ceiling effects. Results of these analyses will be used to further revise items and response scales as necessary. We also will use our pilot testing to develop questions that specifically address social norms and self-efficacy.

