For the remaining dependent variables identified in Table 3, when possible, we will test for differences between the intervention and control using the hierarchical regression approaches above. For rare outcomes for which fewer than 10 total cases are expected, we may be unable to conduct comparative analyses and will instead provide descriptive analyses.

#### Analysis plan and sample size for objective 2

We expect to survey 100 providers at the MEDVAMC in year 2, 100 providers at the MEDVAMC in year 3, and 100 providers at the STVHCS in year 3, resulting in 300 paired pre/post surveys. We will calculate the raw number and proportion of providers at each site whose survey responses exhibit clinically meaningful change (provider learning), as described in Table 2. Though we recognize that this measurement process will be exploratory, we expect the results to shed light on the efficacy of the intervention from a provider perspective, triangulating with improved clinical outcomes from objective 1 and thus augmenting our overall rationale for dissemination. We also intend to explore which of the attributes measured in objective 2 are associated most strongly with changes in clinical outcomes measured in objective 1 and to assess how well any empirical relationships are supported conceptually. Finally, we will assess the empirical relationships between provider learning and provider demographics.

To measure the success of the audit and feedback system, we will document how many episodes of bacteriuria were audited (underwent medical-record review), how many audited episodes resulted in feedback (a phone call or visit to the provider), and how many episodes of feedback were delivered to the correct provider (someone directly involved in the prescribing decisions for the patient). The information about correct delivery of feedback will be particularly important, and we expect the majority of the application barriers to occur in this area. This assessment will be made every three months by the research coordinator. If fewer than 90% of episodes of bacteriuria receive audit, or if fewer than 80% of audits are delivered to the correct team within three days, we will reassess our audit and feedback methods. These evaluation elements will be critical for developing implementation and dissemination protocols.

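### Table 2 counts change on the agreement items only as disagree-to-agree crossings, so many real shifts are lost; a full-scale change score and a scenario total would recover them at almost no cost

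*Protocol article*

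**What the plan says.** Table 2 (protocol article, Development of intervention components) sets a measure of meaningful change for each survey domain.

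- KF2-KF8 and AA1-AA2, nine items in all: "Raw number and proportion of respondents changing from SD or D to SA or A". The footnote names four answers: "A = agree; D = disagree; SA = strongly agree; SD = strongly disagree". A neutral answer is neither listed nor excluded.
- KF1, an ordered four-level recall item: "Average increase from 'do not recall' or 'minimal recall' to 'working familiarity' or 'complete recall".
- KF9 and OE1-OE6: "Raw number and proportion of respondents changing from incorrect to correct answers". The scenario answers are yes/no: "Providers will be asked whether they would or would not treat each case with antibiotics" (Surveys).

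The section Analysis plan and sample size for objective 2 takes these definitions forward: "We will calculate the raw number and proportion of providers at each site whose survey responses exhibit clinically meaningful change (provider learning"). It expects 100 pre/post pairs in each of three site-years and calls the measurement process exploratory. It states no test, significance level, power or effect size. It then plans to relate provider learning to provider demographics, and to "explore which of the attributes measured in objective 2 are associated most strongly with changes in clinical outcomes measured in objective 1".

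The Surveys section says the instrument is still being piloted: "Results of these analyses will be used to further revise items and response scales as necessary".

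**The concern.** The agreement items have ordered answers, and objective 2 is meant to measure increases in knowledge and attitudes. Table 2 turns each pair of answers into one yes/no event: did the respondent cross from the disagree side to the agree side? Movement within a side is not seen. A respondent who starts on the agree side is outside the count altogether, so the measure adds a ceiling of its own wherever baseline agreement is high.

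For the six scenarios, which serve one domain (outcome expectancy), no summary across scenarios is provided.

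At stake is a real but modest improvement in familiarity or acceptance going unseen with about 100 pairs per site-year. Objective 2 stands under Primary objectives and hypotheses with a directional hypothesis, and its results are meant to support those of objective 1 and the case for dissemination.

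**Working it through.** **The plan's own figure.** 100 + 100 + 100 = 300 paired surveys, as stated. Objective 2 has no power figure to reproduce.

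**Inputs.** From the article: 100 pairs per site-year, the SD/D to SA/A rule, and four named categories. Assumed: normally distributed latent answers, a pre/post correlation of 0.5 (0.7 as a second value), shifts of 0.3, 0.5 and 0.8 SD, four or five categories, three baseline distributions, and two-sided 5% tests.

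**Step 1: share of upward moves that Table 2 counts.** Share kept = P(crossing up) / P(any upward move). At correlation 0.5 and a 0.3 SD shift:

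| Scale and baseline (% from SD to SA) | Any upward move | Crossing | Share kept |
|---|---|---|---|
| 4-point, 15/35/35/15 | 0.395 | 0.230 | 58% |
| 4-point, 25/45/25/5 | 0.377 | 0.217 | 57% |
| 4-point, 5/20/50/25 | 0.349 | 0.161 | 46% |
| 5-point, 10/25/30/25/10 | 0.437 | 0.087 | 20% |
| 5-point, 20/35/25/15/5 | 0.433 | 0.090 | 21% |
| 5-point, 5/15/20/40/20 | 0.408 | 0.088 | 22% |

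Over both correlations and all three shifts, 39-64% is kept on four categories, so 36-61% is lost. On five categories 13-29% is kept, so 71-87% is lost.

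**Step 2: power per item with 100 pairs, correlation 0.5.** Crossings are tested by exact McNemar and the full scale by Wilcoxon signed-rank. Reverse crossings are included so that the test is valid, although Table 2 does not count them.

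| Shift | Crossings, 4-point | Crossings, 5-point | Full ordinal scale |
|---|---|---|---|
| 0.3 SD | 34-44% | 21-31% | 69-76% |
| 0.5 SD | 75-90% | 59-72% | 99-100% |

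Repeat runs at 0.3 SD gave 24-46% for crossings and 67-77% for the full scale.

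**Step 3: hand check with a less conservative test.** For uncorrected McNemar, with u the upward and v the reverse crossing probability, power is about Φ{[√n(u − v) − 1.96√(u + v)] / √[(u + v) − (u − v)²]}.

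- 4-point symmetric, u = 0.230, v = 0.112: (1.180 − 1.146) / 0.573 = 0.059, so power is about 52%. The exact test gave 44% and the full scale 74%.
- 5-point symmetric, u = 0.087, v = 0.031: (0.560 − 0.673) / 0.339 = −0.334, so power is about 37%. The exact test gave 27% and the full scale 76%.

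The choice of McNemar version moves the crossing figure by about 10 points and does not close the gap.

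**Step 4: scenarios.** Assumed: 50% correct at baseline, within-person item correlation 0.2 or 0.4, and pre/post correlation of the underlying trait 0.7. With a latent shift of 0.25, one scenario has 28-29% power (McNemar) and the 0-6 total 90-91% (paired t-test). With a shift of 0.4 the figures are 59-65% and about 100%.

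**The case against.** Four arguments deserve weight.

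*The measure is exploratory and no test is planned.* This is correct. The power figures describe how much information the measure holds; they do not show a planned test failing. The raw paired answers are collected, so a fuller analysis remains possible later. This lowers the severity. It does not remove the point, because the cut is a stated choice and the article mentions no full-scale measure.

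*A disagree-to-agree conversion is a readable responder definition.* This also stands, and it is a reason to keep the counts. It is not a reason to have only the counts.

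*Piloting will look for floor and ceiling effects and may revise the response scales.* That may help with badly placed items. It does not change the rule that a provider who already agrees cannot register a gain.

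*Scenario results by item have a purpose.* The Surveys section wants to learn which case features drive the decision to treat, and a total alone would hide that. The total therefore belongs beside the item results.

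A reader might also infer more than the text supports:

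- That most real shifts are discarded. On the four named categories with a symmetric or disagree-heavy baseline, 52-64% of upward moves are kept. Most are lost only if answers already lean to agree or a neutral option exists, and the article establishes neither.
- That OE1-OE6 will be scored item by item. The row is silent on how they are combined, and that detail may sit in a fuller plan. The answers are yes/no, so no upward shift on an item is discarded; what a missing total costs is power.
- That KF1 is a crossing count. Its row speaks of an average increase, which is ambiguous.
- That the yes/no learning variable is the one to be related to clinical outcomes. The article names provider learning only in the demographics analysis; for clinical outcomes it speaks of the attributes measured.

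**Conclusion.** The point holds for KF2-KF8 and AA1-AA2: the stated measure ignores within-side movement and any move to or from a neutral option, and it gives providers who already agree no way to show improvement. For OE1-OE6 the supported statement is only that Table 2 provides no total score.

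The step 2 and step 4 figures rest wholly on assumed shifts, correlations and baselines; only the 100 pairs comes from the article. For a modest 0.3 SD shift the full scale has roughly twice the power of crossings, or more. At 0.5 SD on four categories the gap shrinks to about 10-25 points. This is a minor, worthwhile improvement to an exploratory analysis, and not a flaw that invalidates objective 2.

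**What to change.** In Table 2 and the objective 2 analysis section:

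1. For KF2-KF8 and AA1-AA2, make the measure the paired change in the full ordinal score, by item or as a domain mean, analysed by a signed-rank test or an ordinal mixed model.
2. For OE1-OE6, keep the item-level results and add the paired change in the number of scenarios correct (0-6).
3. Use these scores in the analyses against provider demographics and clinical outcomes.
4. State whether the average increase for KF1 is taken on its four-level scale.
5. Keep the SD/D to SA/A counts as a descriptive summary.

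The cost is wording only: the surveys, respondents and number of pairs stay the same, and the instrument is still in development. The small downside is that a score change is harder to read than a count of converted providers, which is why the count stays.

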#### Diagnostic algorithm

The purpose of the diagnostic algorithm is to operationalize the 53-page CAUTI guidelines and the 11-page ABU guidelines so that healthcare providers can determine how to apply these guidelines to their patients. This algorithm will also be used by research personnel at both sites to classify episodes of bacteriuria as CAUTI or ABU and to determine whether use of antibiotics for the bacteriuria was appropriate or inappropriate. This algorithm has been reviewed and modified in accordance with the comments of 8 of 11 experts on the guidelines panel to establish evidence of content validity and is currently being assessed by cognitive interviewing with the target population of healthcare providers to establish evidence of construct validity. Further validation efforts will include testing convergent and predictive validity.

#### Audit and feedback intervention

The audit and feedback intervention design is closely linked to the diagnostic algorithm. We are preparing a script and a visual aid based upon the diagnostic algorithm and the various decision points in this algorithm. Individualized audit and feedback will be provided to medical residents during their ward team's designated educational time and to healthcare providers in the extended-care line during charting time. Prior to an audit and feedback visit, the research personnel will prepare a color-coded version of the algorithm that indicates where appropriate actions were taken for the episode of bacteriuria (green), where decisions were inappropriate (red), and which decision path would have been guidelines compliant (blue). An individualized audit and feedback script will be generated that covers only the decision nodes relevant to the case. This script will be presented both in PowerPoint (Microsoft Corporation, Seattle, WA, USA) and on paper for discussion. The paper copy of the color-coded algorithm will be given to the healthcare provider to review, while the contents of the script are delivered verbally by the research assistant. The information content and delivery have been carefully designed to be supportive rather than punitive, and to provide the correct answer at each decision node. The delivery of the audit and feedback script and the color-coded algorithm will be pilot tested with residents who will graduate prior to the start of the intervention and with nonphysician healthcare providers on nonstudy wards.

Ward- and/or team-level feedback will be prepared and delivered on a monthly basis in the form of colorful pie charts depicting the percentage of bacteriuria treatment decisions that were or were not guidelines compliant and how each team's performance compares to that of other teams. Our study logo will appear on all study materials to facilitate awareness and recognition of our campaign.

#### Outcomes

Objective 1 focuses on the clinical outcomes of inappropriate screening for and treatment of catheter-associated ABU, as well as on complications of inappropriately prescribed antibiotics (Table 3). Objective 2 focuses on measuring changes in knowledge and attitudes concerning the ABU and CAUTI guidelines (see Table 2).

**Table 3 T3:** clinical outcomes for objective 1 in order of importance

Outcomes	**Measurement of change**^**a**^
Inappropriate treatment of CAABU	Fewer episodes of CAABU treated inappropriately

Inappropriate collection of urine cultures from patients with CAABU	Decreased number of urine cultures/1,000 catheter-days

Number of days antibiotics given for CAABU	Fewer days of antibiotic use for CAABU

Use of urinary catheters	Decreased urinary catheter-days/patient bed-days

Complications of inappropriate antibiotics	*Clostridium difficile *colitis, emergence of resistant organisms^b^

Complications of bacteriuria	No increase in pyelonephritis or urosepsis

^a^Comparisons are for the specific wards on the intervention facility and the corresponding wards on the control facility. ^b^In 30 days following inappropriate antibiotic use in a given patient.

CAABU = catheter-associated asymptomatic bacteriuria.

### Data collection

#### Surveillance of target hospital wards

Surveillance of all targeted hospital wards will include regular, systematic chart reviews of medical and nursing notes to identify each patient with a urinary catheter, each urine culture ordered on those patients, and the ordering of antibiotics after urine culture results are reported. Research personnel have been trained to follow a systematic process of documentation for each of these measures (described in Table 3), which has been validated against bedside observation.

#### Surveys

The survey instrument was created through literature review, review of existing antimicrobial stewardship projects, and discussion with investigators conducting related studies, including studies of UTI and ABU [28-33]. The survey contains items that measure knowledge of the guidelines and their contents, as well as items that measure attitudes and outcome expectancies related to the guidelines. No standardized instrument is available to assess physician-related barriers to appropriate management of ABU. Our starting point was prior surveys of management of hypertension [31] and antibiotic-prescribing decisions for pneumonia [29]. We also found several qualitative studies concerning prevention of CAUTI [34,35] and inappropriate use of urinary catheters [36]. Two projects addressing unnecessary antibiotic use were also relevant: the "Do Bugs Need Drugs" project in Canada [37] and the postprescription antimicrobial review study mentioned in our Background section above [38]. The principal investigator contacted the authors of these studies by email, by telephone, and/or in person at national meetings to discuss appropriate survey design.

The survey instrument will have three sections. The first section will be a cover letter. The cover letter explains the purpose of the study to the healthcare providers and explains that their participation is entirely voluntary, thus satisfying implied consent for participation. The second part of the survey is a cover sheet that assesses provider demographics, such as level of training, type of training, etc. This cover sheet will have a randomly generated number on it that will also appear on each subsequent sheet of the survey. The cover sheet with the provider's identifiable information can then be separated from the surveys to avoid bias in interpretation of survey results. The third section of the survey contains the survey questions. These questions will assess knowledge: degree of awareness of the existence of the guidelines, familiarity with the guidelines' content, and confidence in that familiarity. Other questions will measure physicians' acceptance of the guidelines, and we have also designed short patient scenarios to assess outcome expectancy about the guidelines. Each case will present a hospitalized patient with bacteriuria and a chronic, indwelling urinary catheter. The cases will differ in elements, such as the level of pyuria, the patient's age and comorbidities, the type of organism isolated from the urine, the appearance or smell of the urine, the presence of specific urinary symptoms, and the presence of vague systemic complaints. Providers will be asked whether they would or would not treat each case with antibiotics. These cases are designed to address providers' beliefs about the consequences of not treating bacteriuria (risk perception) and to elucidate which elements drive the decision to treat/not treat bacteriuria.

Although we have built our survey on established models concerning antibiotic prescribing decisions, [29] our survey instrument has been tailored to our specific clinical issue (CAUTI) and, thus, will require pilot testing with a selection of participants from the targeted groups of healthcare providers. We plan to conduct cognitive interviews to assess clarity of wording, understandability of items, and appropriateness of response options. We will conduct preliminary analyses of responses given, response-option use frequency, and floor/ceiling effects. Results of these analyses will be used to further revise items and response scales as necessary. We also will use our pilot testing to develop questions that specifically address social norms and self-efficacy.

#### Monitoring the success of the intervention

We plan to monitor the success of the intervention as we proceed, which in itself is crucial to interpreting the outcomes and ultimately disseminating the intervention to other sites. We will administer brief exit interviews when giving the postintervention surveys in years 2 and 3 (Table 2). In these interviews, we will informally assess and address barriers to implementation that may arise during the course of the study by asking providers about their perception of the implementation efforts. Although we do not expect these information surveys to result in quantifiable data, they will help us customize our intervention to local conditions in the various hospital units.

